#### Cost-utility analysis

Taking a previous study by our group as a reference [90], the cost-utility of TAU + MBSR compared to the other study arms will be evaluated from healthcare and societal perspectives.

Costs will be estimated from the healthcare and societal perspectives during the 12 months of follow-up. Direct health care costs are calculated by adding costs derived from medication consumption, medical tests, use of health-related services, and cost of staff to run the intervention. The cost of medication is calculated by determining the price per milligram during the study, according to the Vademecum International (Red Book), and including value-added tax. Total costs of medications are calculated by multiplying the price per milligram by the daily dose in milligrams and the number of days receiving such treatment. The unit costs of medical tests and health services will be obtained from the SOIKOS health database (http://www.oblikue.com/bddcostes/). Indirect costs are calculated by taking the number of days on sick leave and multiplying it by the minimum daily wage in Spain. Finally, total costs are calculated by adding direct and indirect costs. The utilities represent the rating of the patients’ quality of life on a scale from 0 (as bad as death) to 1 (perfect health). QALYs will be calculated using Spanish EQ-5D-5L tariffs.

First, we will use a micro-costing approach, which involves careful specification of training costs, staffing costs, venue overheads, materials, and staff travel. Then, following the International Society for Pharmacoeconomics and Outcomes Research (ISPOR) core recommendations for cost-effectiveness analyses alongside RCTs [91], we will calculate the incremental cost-utility ratios, defined as the difference in mean costs divided by the difference in mean QALYs. As the duration of the study is 12 months, neither costs nor outcomes are subject to discounting. QALYs gained in each evaluation are approximated by using the area under-the-curve technique. To gain insight into the uncertainty around the pooled mean ICUR, we will plot the pooled bootstrapped cost-effect pairs on cost-utility planes. Finally, acceptability curves will be presented which represent the probability that the intervention is cost-effective, given a varying threshold for the willingness to pay for each QALY gained. The robustness of the cost-utility results will also be tested by computing distinct sensitivity analyses. For instance, we will perform a per protocol analysis from which the FMS patients who do not attend at least 6 MBSR or FibroQoL sessions will be excluded.

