### Participants

A total of 180 FMS patients will be recruited from the Rheumatology service at Sant Joan de Déu Hospital (St. Boi de Llobregat, Spain). Sample size is established on the basis of a previous meta-analysis of controlled MBSR trials [45] in which a mean effect size of *d* = 0.53 was found. This effect size results in 1-b = 0.89 (alpha = 0.05) for *N* = 60 patients per group (180 patients overall). With 20 % maximal attrition, the power remains 1-b = 0.82. The estimated sample size for the study of biomarkers (neuroimaging and cytokines) was 30 participants per condition, this sample size is considered adequate given that approximately 20–40 participants (in between-group designs) are necessary to detect a change of 15 % in cerebral blood flow in regions of interest (ROI) by means of pseudo-continuous Arterial Spin Labeling (pCASL) [46].

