### Procedure

The potential FMS participants will be screened through an initial telephonic interview by one of the authors ([name]), who will provide a general overview of the study. Subsequently, two highly trained clinical psychologists (not involved with the treatment and blind to group allocation) will make an appointment with those patients who met the inclusion criteria and agreed to participate in the study. The psychologists will check all inclusion/exclusion criteria (both general and additional for the biomarkers study) and will perform all face-to face interviews. As mentioned above, study participants will be randomised to one of the three conditions (i.e., TAU, TAU + MBSR, TAU + FibroQoL). Both MBSR and FibroQoL are conducted in a group format (up to 15 people in each group). To balance the number of participants eligible for the biomarkers sub-study across the three arms, stratified randomisation will be performed. The proportion of eligible participants for the biomarkers evaluation and those only meeting criteria for the general study will be pre-fixed at 1:1 in all samples. Four treatment waves (*N* = 45 each) will be carried out to achieve the required final sample (*N* = 180).

Three-five days after the clinical evaluation, patients assigned to the biomarkers sub-study will be contacted for blood extraction and MRI completion. To minimise circadian variability in immunological markers, all whole blood samples will be collected between 8–9 am. Interventions will be conducted using a parallel design to reduce seasonal variability in the study measures. The participants will be interviewed at baseline, after treatment, and at 12-month follow-up (56 weeks after randomisation). The neuroimaging tests and cytokine measurements will be performed at baseline and after treatment. A flowchart of participants is displayed in Fig. 1.

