#### Secondary outcome measures and process measures

The *Fibromyalgia Survey Diagnostic Criteria* (FSDC) [59, 60] is a 6-item self-report questionnaire that registers the key symptoms of FMS according to the latest revision of the ACR. It includes assessment through the Widespread Pain Index (WPI) identifying 19 body areas (jaws, shoulders, upper arms, lower arms, hips, upper legs, lower legs, neck, chest, upper back, lower back and abdomen) where pain or tenderness was felt during the previous 7 days (total score 0–19). The Symptom Severity Scale (SS; range from 0–12) includes three major symptoms (fatigue, trouble thinking/remembering and waking up tired or unrefreshed), which is scored from 0 to 3, as well as three additional symptoms (pain or cramps in lower abdomen, depression, headache), which can be coded as present (1) or absent (0). The fibromyalgianess scale is defined as the sum of the WPI items (0–19) and the 6-item SS scale (0–12), so total scores can range from 0 to 31.The *Client Service Receipt Inventory* (CSRI) [61, 62] used for the present project will be designed to collect retrospective data on medication and service receipt: 1. Medication. A profile of the patient’s use of all prescribed medications (analgesics, non-steroidal anti-inflammatories, short- and long-acting opioids, etc.) will be requested, including the name of the drug, the prescriber, the dosage level, the total number of days taking the drug, the total dosage consumed, the reasons for changing the drug, and adherence. 2. Service receipt. We will collect information about emergency services, general medical in-patient hospital admissions and out-patient health care services. Patients will also be asked about type and number of diagnostic tests administered. As shown in Table 3, the CSRI will be administered at baseline and at a 12-month follow-up*; on both occasions, the previous 12 months will be reviewed*.The *EuroQoL-5D questionnaire* (EQ-5D-5L) [63] is a widely used health-related quality of life instrument with a non-disease-specific classification system composed of 2 parts: Part 1 is a self-reported description of health problems classified into five dimensions. Patients mark one of five degrees of severity in each dimension. The time frame is the day of responding. Part 2 records the current subject’s health on a Visual Analogue Scale (VAS); a vertical 10 cm line on which the best and worst imaginable health states score 100 and 0, respectively.The *Hospital Anxiety and Depression Scale* (HADS) [64, 65] was originally developed to quantify the severity of anxiety and depressive symptoms in non-psychiatric hospital patients The HADS includes a total of 14 items that assess anxiety (HADS-A) and depressive (HADS-D) symptoms, with 7 items in each subscale. Each item is answered on a four-point (0-to-3) scale so that possible scores range from 0 to 21 for both anxiety and depressive symptoms, with higher scores indicating greater severity.The *Perceived Stress Scale* (PSS-10) [66] is a 10-item, self-administered instrument that measures the degree to which situations in one’s life are considered stressful. Scores range from 0 to 72. The Spanish version of the PSS-10 has adequate reliability and validity [67].The *Multidimensional Inventory of Subjective Cognitive Impairment* (MISCI) [68] is a 10-item measure of perception of cognitive dysfunction in FMS, developed through classical test theory and item response theory from cognitive functioning item banks that were developed as part of the Patient Reported Outcomes Measurement Information System (PROMIS). The MISCI showed excellent internal reliability, low ceiling/floor effects, and good convergent validity with a similar measure.The *Pain Catastrophising Scale* (PCS) [69, 70] is a 13-item questionnaire derived partially from the Coping Strategies Questionnaire and other descriptions of catastrophising. It has three dimensions: Rumination (tendency to focus excessively on pain sensations), Magnification (tendency to magnify the threat value of pain sensations) and Helplessness (tendency to perceive oneself as unable to control the intensity of pain). The PCS total score and subscale scores are computed as the algebraic sum of ratings made for each item. PCS items are rated in relation to frequency of occurrence on 5-point scales (0 = never ~ 4 = almost always).The *Five Facet Mindfulness Questionnaire* (FFMQ) [71, 72] consists of 39 items that assess five facets of mindfulness. Items are rated on a Likert scale ranging from 1 (never or very rarely true) to 5 (very often or always true). The factors include: *Observing*, including noticing or attending to internal and external experiences such as sensations, thoughts, or emotions. *Describing* refers to labelling internal experiences with words. *Acting with awareness* involves focusing on one’s activities in the here and now as opposed to behaving mechanically. *Non-judging of inner experience* refers to taking a non-evaluative stance toward thoughts and feelings. Finally, *non-reactivity to inner experience* is allowing thoughts and feelings to come and go, without getting caught up in or carried away by them. In a recent online survey answered by 4,986 FMS patients from all 50 US states and 30 countries, the FFMQ subscales was shown to discriminate well among FMS patients self-identified as meditators or non-meditators. Overall, FMS patients with higher mindfulness scores had lower levels of FMS symptom severity as measured with the FIQR [73].The *Self-Compassion Scale-short form* (SCS-12) [74, 75] is a shorter version (12 items) of the SCS (26 items). The SCS was designed to assess overall self-compassion (total score) and components of self-compassion across three dimensions: common humanity, mindfulness and self-kindness. The SCS–SF shows good internal consistency (Cronbach’s α ≥0.86) and very high convergence with the long form of the scale (r ≥0.97).The *Psychological inflexibility in pain scale* (PIPS) [76, 77] is a 12-item scale designed to measure psychological inflexibility in pain patients. The instrument includes two factors: *avoidance* and *cognitive fusion* related to pain. The items consist of different statements that are considered to be related to chronic pain, psychological inflexibility, suffering and disability (coherent with the ACT theory). All the items are rated on a 7-point Likert-type scale that ranges from “1 = never true” to “7 = always true”, with higher scores indicating more psychological inflexibility.

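### The cost-utility analysis gives no role to prior-year cost, although the baseline CSRI supplies direct healthcare use over a matching 12-month window, so available precision is left unused

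*Protocol article*

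**What the plan says.** The Cost-utility analysis section of the protocol article sets the window: "Costs will be estimated from the healthcare and societal perspectives during the 12 months of follow-up". It will then report "incremental cost-utility ratios, defined as the difference in mean costs divided by the difference in mean QALYs". For uncertainty, "we will plot the pooled bootstrapped cost-effect pairs on cost-utility planes", followed by acceptability curves and sensitivity analyses, of which a per-protocol analysis is the one named. No regression, covariate or baseline cost appears in the section.

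The CSRI is scheduled at baseline and at 12 months (Table 3). The Secondary outcome measures section adds that "on both occasions, the previous 12 months will be reviewed". The instrument "will be designed to collect retrospective data on medication and service receipt", which includes emergency, in-patient and out-patient care and diagnostic tests. Sick leave is not among the items listed.

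The societal perspective adds a further component: "Indirect costs are calculated by taking the number of days on sick leave and multiplying it by the minimum daily wage in Spain". The article does not say which instrument records those days or over what period.

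On allocation, the Procedure section states: "To balance the number of participants eligible for the biomarkers sub-study across the three arms, stratified randomisation will be performed". No other stratification factor is named, so prior cost is not balanced by design.

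**The concern.** The trial collects, before treatment, a measure of resource use over a window of the same length as the one that produces the outcome cost. In a chronic condition, one would expect a heavy user in the year before baseline often to be a heavy user in the year after. Comparing follow-up means alone leaves that predictable variation in the error term. It also lets part of any chance difference in prior use between arms appear as a cost effect of treatment.

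Cost-utility belongs to the first objective of the trial. The incremental cost enters the ICUR, the cost-utility planes and the acceptability curves, and each would be less precise than the collected data allow.

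**Working it through.** **Inputs from the article.** 60 patients per arm, or 48 after the stated 20 % attrition (60 × 0.8 = 48), from the Participants section. The estimator, the cost window and the CSRI look-back are as described above. The article gives no cost SD, target cost difference or correlation between prior-year and follow-up cost, so there is no cost figure to reproduce. Its power statement concerns a clinical effect size and does not bear on this point.

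**Assumption.** rho, the correlation between prior-year and follow-up cost, is taken as 0.3, 0.5 and 0.7. All results are in SD units of cost.

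**Step 1: precision of the unadjusted difference.** SE = SD × √(2/n).
- n = 60: √(2/60) = 0.183 SD
- n = 48: √(2/48) = 0.204 SD

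**Step 2: effect of adjustment.** Adjusting for baseline cost multiplies the variance by (1 − rho²) and the SE by √(1 − rho²). The equivalent unadjusted sample size is 60/(1 − rho²).

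| rho | 1 − rho² | SE ratio | Equivalent n per arm | Adjusted SE, n = 60 | Adjusted SE, n = 48 |
|---|---|---|---|---|---|
| 0.3 | 0.91 | 0.954 | 65.9 | 0.174 | 0.195 |
| 0.5 | 0.75 | 0.866 | 80.0 | 0.158 | 0.177 |
| 0.7 | 0.51 | 0.714 | 117.6 | 0.130 | 0.146 |

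**Step 3: how much of a chance imbalance carries over.** A baseline imbalance of I SD moves the expected unadjusted follow-up difference by rho × I. One SE of imbalance at 60 per arm is 0.183 SD, so the shift is:
- rho 0.3: 0.3 × 0.183 = 0.055 SD
- rho 0.5: 0.5 × 0.183 = 0.091 SD
- rho 0.7: 0.7 × 0.183 = 0.128 SD

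For any one pair of arms, the chance of an imbalance above 0.2 SD in either direction is about 27 % (0.2/0.183 = 1.095, two-sided normal tail 0.273).

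**Step 4: does skewness change this?** In a simulation with lognormal costs (coefficient of variation 1, rho set on the cost scale, 60 per arm, 10,000 runs, slope estimated in each run), the SE ratios were 0.96, 0.85 and 0.69 at rho 0.3, 0.5 and 0.7. These are close to the formula. Both estimators had a mean error of about zero (within 0.003 SD).

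**The case against.** The quoted definition is the generic one for an incremental ratio, and a regression-adjusted cost difference is also a difference in mean costs. The article does not call it raw or unadjusted. It cites an earlier study by the same group and published recommendations as its models, and a full protocol or analysis plan may name covariates. This stands in part: the lack of adjustment is the natural reading of the section, not an express commitment. But the article defines the estimator, the cost window and the uncertainty method and gives the baseline CSRI no place among them. The suggestion improves on that stated estimator and does not merely ask for more detail.

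Baseline CSRI data may be used elsewhere: all baseline measures are compared between arms, and mixed models are planned for each secondary outcome, among which Table 3 lists the CSRI. Neither feeds into the ICUR, which is defined separately.

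Three stronger readings are tempting, and the documents do not support them.
- **The incremental cost is biased or its bootstrap invalid.** Under randomisation the unadjusted difference is unbiased, and the bootstrap already carries the extra variance. Only the fraction rho of an imbalance passes through.
- **Every patient has a matching prior-year societal cost.** The CSRI as described lists medication and services, not sick leave. A matching baseline is therefore established for the healthcare perspective only.
- **The trial loses power for a cost comparison.** The section plans ratios, planes and acceptability curves, not a test of the cost difference, so a power gain would describe an analysis that is not planned.

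**Conclusion.** The point holds as one about efficiency and conditional accuracy. As described, the incremental cost compares follow-up means and leaves unused a baseline measure of direct healthcare use with the same look-back. The estimate remains valid but is less precise than it could be.

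The size rests entirely on the assumed rho. At 0.3 or below the SE falls by 5 % or less, which is minor. At 0.5 it falls by about 13 %, equivalent to 80 patients per arm in place of 60. At 0.7 it falls by about 29 %, equivalent to about 118 per arm. These figures describe the cost difference alone. The gain in the ICUR and the acceptability curves also depends on the QALY difference and its correlation with cost, and was not calculated.

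**What to change.** State in the Cost-utility analysis section that the incremental cost is estimated by regressing follow-up cost on arm and baseline 12-month CSRI direct healthcare cost, within each bootstrap replicate and jointly with the QALY equation. Use the adjusted difference in the ICUR, the planes and the acceptability curves, and keep the unadjusted difference as a sensitivity analysis.

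For the societal perspective, use prior-year direct healthcare cost as the covariate. State whether baseline sick leave is recorded, and add its cost to the model only if it is.

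For the healthcare perspective this changes analysis wording only, with no new visit, instrument or patient. The small cost is that baseline resource use must be valued with the same unit costs as follow-up use.

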**Methods:**

Effectiveness, cost-utility, and neurobiological analyses performed alongside a 12-month RCT. The participants will be 180 adult patients with FMS recruited at the Sant Joan de Déu hospital (St. Boi de Llobregat, Spain), randomly allocated to one of the three study arms: TAU + MBSR vs. TAU + FibroQol vs. TAU. A comprehensive assessment to collect functional, quality of life, distress, costs, and psychological variables will be conducted pre-, post-intervention, and at 12-month post-intervention. Fifty per cent of study participants will be evaluated at pre- and post-treatment using Voxel-Based Morphometry, Diffusion Tensor Imaging, pseudo-continuous Arterial Spin Labeling, and resting state fMRI. A cytokine multiplex kit of high-sensitivity will be applied (cytokines IL-6, IL-8, IL-10 + high-sensitivity CRP test).

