### Study measures

Study participants will complete the following instruments as part of a paper-and-pencil battery of measures (see Table 3):*Sociodemographic-clinical questionnaire*. The following information will be collected: gender, age, ethnic group, marital status, living arrangements, educational level, employment status, and annual income. Relevant clinical variables, such as family and personal medical history, years of FMS diagnosis and comorbid conditions will also be assessed.

**Table 3 Tab3:** Study periods at which measures and data are collected

Study measures	Baseline	During treatment	2 months	12-months
Demographic information (gender, age, etc.)	X			
History of FMS (years of illness)	X			
Contact details	X			
SCID-I (depression module)	X			
*Screening measures*				
MMSE (cognitive impairment)	X			
*Primary outcome measure*				
FIQR (functional impairment)	X		X	X
*Secondary outcome measures*				
FSDC (fibromyalginess)	X		X	X
HADS (anxiety and depression)	X		X	X
PSS-10 (perceived stress)	X		X	X
MISCI (subjective cognitive impairment)	X		X	X
EQ-5D-5L (quality of life)	X			X
CSRI (health economic evaluation)	X			X
FFMQ^a^ (mindfulness facets)	X		X	X
PCS^a^ (pain catastrophizing)	X		X	X
PIPS^a^ (psychological inflexibility)	X		X	X
SCS-12^a^ (self-compassion)	X		X	X
*Other measures*				
Structural + Functional Neuroimaging data	X		X	
Inflammatory data	X		X	
CEQ (Expectation/Satisfaction with treatment)	X (EXP)		X (SAT)	
PGIC & PSIC (Impression of change)			X	X
Treatment attendance form: Attendance at each scheduled MBSR/FibroQoL session		X		
Log of MBSR and FibroQoL practices		X		
Treatment fidelity (review of video-taped MBSR sessions) & monitoring of adverse events		X	X	X

*CEQ* Credibility/Expectancy Questionnaire, *CSRI* Client Service Receipt Inventory, *EQ-5D-5L* EuroQoL questionnaire, *FFMQ* Five Facet Mindfulness Questionnaire, *FIQR* Revised Fibromyalgia Impact Questionnaire, *FSDC* Fibromyalgia Survey Diagnostic Criteria, *HADS* Hospital Anxiety and Depression Scale, *MISCI* Multidimensional Inventory of Subjective Cognitive Impairment, *MMSE* Mini-Mental State Examination, *PCS* Pain Catastrophizing Scale, *PGIC & PSIC* Patient Global and Specific Impression of Change, respectively, *PIPS* Psychological Inflexibility in Pain Scale, *PSS-10* Perceived Stress Scale, *SCID-I* Structured Clinical Interview for DSM Axis I Disorders, *SCS-12* Self-Compassion Scale

^a^Secondary outcome measures that also considered process variables

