#### Analysis of clinical efficacy

To assess treatment effects, we will perform Intention-to-Treat analyses, which will include all participants who undergo random allocation, using multiple imputation to replace missing values.

To study the differences in the primary outcome and in each of the secondary outcomes between groups, linear mixed-effects models [85] will be prepared using Restricted Maximum Likelihood to estimate the parameters. Comparisons amongst treatment groups at post-treatment and at 12-month follow-up will be computed with estimates derived from the linear mixed-effect models (use of the Bonferroni method to adjust the significance level of the pairwise contrasts). Calculations of between-groups effect sizes using Cohen’s *d* with its 95 % confidence interval will be based on the pooled standard deviation at baseline. Finally, to make the findings from the present RCT meaningful to clinicians, the number-needed-to-treat (NNT) [86] in the MBSR condition will be reported. Taking the Luciano et al. [87] NNT approach as our reference, we dichotomise participants into responders or non-responders using three separate cut-off criteria: (a) ≥ 20 % reduction on the FIQR total score from baseline to post-treatment; (b) ≥ 50 % reduction on the FIQR total score from baseline to post-treatment; and (c) number of patients crossing a cut-off point (reaching no worse than mild functional impairment; FIQR total score < 39).

Given that some pharmacological treatments may interfere with cytokine levels [88], differences in cytokine levels between patients taking vs. not taking antidepressants will be evaluated.

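### Table 3 gives the EQ-5D-5L no post-treatment measurement, against the Abstract and the efficacy analysis, so the area-under-the-curve QALY is one straight line that probably understates gains over TAU

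*Protocol article*

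**What the plan says.** The Cost-utility analysis section derives utilities from Spanish EQ-5D-5L tariffs and says that "QALYs gained in each evaluation are approximated by using the area under-the-curve technique". The incremental ratio is "defined as the difference in mean costs divided by the difference in mean QALYs".

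Table 3 has the columns "Study measures Baseline During treatment 2 months 12-months". The EQ-5D-5L row has two marks, under baseline and 12 months: "EQ-5D-5L (quality of life) X X". The primary outcome has three, including 2 months: "FIQR (functional impairment) X X X". Apart from the EQ-5D-5L, every secondary outcome except the CSRI (service use and costs) is also marked at 2 months. The section on secondary and process measures explains the CSRI gap: it is given twice and looks back over 12 months each time. The same section says the EQ-5D-5L refers to the day on which it is answered.

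Two other places imply a post-treatment value. The Abstract says: "A comprehensive assessment to collect functional, quality of life, distress, costs, and psychological variables will be conducted pre-, post-intervention, and at 12-month post-intervention". The Analysis of clinical efficacy section models the primary outcome and each secondary outcome, and adds: "Comparisons amongst treatment groups at post-treatment and at 12-month follow-up will be computed". Table 3 lists the EQ-5D-5L among the secondary outcomes.

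**The concern.** Cost-utility is part of the trial's first objective, and the QALY difference is the denominator of its main result. Because the EQ-5D-5L describes a single day, a month-12 score carries no information about the months before it. With only baseline and month 12, the area-under-the-curve method has to assume that any gain starts at zero and grows in a straight line for a year. The programmes last eight weeks, so a gain by about month 2 is plausible, and a straight line would credit only part of it.

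A utility that was not collected at 2 months cannot be recovered by later analysis. Multiple imputation would have no observed 2-month EQ-5D-5L values to draw on. A patient lost before month 12 would contribute no utility after baseline, and the sample-size section allows for attrition of up to 20%.

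**Working it through.** The article states no utility, QALY or cost-utility figure, so there is none to reproduce. The check compares the two-point and three-point areas.

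**Inputs.** EQ-5D-5L at months 0 and 12 (Table 3). An existing visit at month 2 (Table 3), at the end of eight weekly sessions (Interventions). A one-year horizon (Cost-utility analysis). 60 patients per arm (Participants).

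**Formulas.** Let g be the utility gain over control at month 2, and r the share of g that remains at month 12. Lines are straight between visits and there is no baseline difference.

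- Two points: 0.5 × r × g.
- Three points: g × [(2/12)/2 + (10/12) × (1 + r)/2] = g × (0.5 + 0.4167r).
- Share missed: 1 − (two-point ÷ three-point).

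| Share kept at month 12 (r) | Two-point | Three-point | Missed |
|---|---|---|---|
| 1 | 0.500g | 0.917g | 45% |
| 0.75 | 0.375g | 0.813g | 54% |
| 0.5 | 0.250g | 0.708g | 65% |
| 0.25 | 0.125g | 0.604g | 79% |
| 0 | 0 | 0.500g | 100% |

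More than half is missed only when r is below 0.25/(0.5 − 0.2083) = 0.857. The percentages do not depend on g.

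**Illustrative utility gains (assumed; none are in the document).** A gain of 0.06 that is held: 0.030 against 0.055 QALY. A gain of 0.08 fading to 0.04: 0.020 against 0.057. A gain of 0.08 fading to zero: 0 against 0.040.

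**Timing.** The Procedure section puts the 12-month follow-up at 56 weeks after randomisation. With visits at 8 and 56 weeks, the shares missed are 46%, 54%, 65%, 79% and 100%, so the result does not depend on this choice.

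**When the direction reverses.** Let a be the month-2 gain and b the month-12 gain, with b positive. The two-point area is 0.5b and the three-point area is 0.5a + 0.4167b. The two-point area is larger only if 0.5a < 0.0833b, that is, a < b/6. Example: a = 0 and b = 0.06 give 0.030 against 0.025.

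**Baseline utility.** Its direct weight in the QALY is 1/2 with two points and (2/12)/2 = 1/12 with three. The utility SD is not given. Assuming 0.15 to 0.30, the standard error of a chance baseline difference is SD × √(2/60) = 0.027 to 0.055. Half of that, 0.014 to 0.027 QALY, enters a two-point contrast directly. If baseline and month-12 scores have equal SDs and an assumed correlation of 0.5, the two-point QALY has an SD of √(1.5/2) = 0.866 utility SDs unadjusted, and 0.5 × √(1 − 0.25) = 0.433 after adjustment for baseline utility.

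**The case against.** - **Size.** A reader might infer that the straight line loses most of any gain. It does not: a fully sustained gain loses 45%, and the loss passes one half only once about 14% of the gain has faded.
- **Direction.** A reader might also infer that understatement is certain. The article describes MBSR as a skill built by repeated practice, including at home, so a slow build-up is possible, and a late enough gain would be overstated. This stands, but it requires a month-2 gain below one sixth of the month-12 gain.
- **Comparator.** The argument runs against TAU. Between MBSR and FibroQoL both arms are interpolated in the same way, and no direction can be given without their time courses. This stands.
- **Schedule conflict.** The Abstract sentence is a pooled list. It also implies post-treatment costs, which the CSRI description rules out. The efficacy sentence is equally general. So the text may be loose rather than a rival schedule. That is fair, but it leaves Table 3 as the only specific statement, and on that reading the 2-month utility is not collected.
- **Baseline imbalance.** A reader might take the ratio's definition as a commitment to an unadjusted, biased contrast. The article gives only the ordinary definition and does not say the difference is unadjusted. Adjustment may be set in an analysis plan that is not shown. Under randomisation the imbalance is chance and costs precision; it is not systematic bias.
- **Scope.** The primary outcome, the FIQR, is measured at all three visits, so no conclusion on it is affected.

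**Conclusion.** The point holds in a bounded form. The Abstract and the efficacy section imply a post-treatment EQ-5D-5L that Table 3 does not provide. On the Table 3 schedule, the QALY is one trapezoid that cannot register the course after treatment.

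If the gain is present by about month 2, the loss is about 45% when it is sustained, about 65% when half is kept, and complete when it has faded by month 12. In the sustained case, with a positive cost difference, the incremental ratio is inflated by 0.917/0.500 = 1.83. QALY gains of MBSR and FibroQoL over TAU are therefore likely to be understated. The direction for MBSR versus FibroQoL is open.

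These figures assume straight lines between visits and an early effect. The document does not fix the trajectory. Baseline adjustment is a precision improvement and not a separate defect.

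**What to change.** 1. Reconcile Table 3 with the Abstract and the Analysis of clinical efficacy section. If a post-treatment EQ-5D-5L is already intended, correct the Table 3 row; if not, add it at the existing 2-month visit.
2. State that QALYs are computed from three points, using each patient's actual visit dates.
3. As a free improvement in precision, estimate incremental QALYs by regression on arm with baseline utility as a covariate. The third time point by itself reduces the direct baseline weight from 1/2 to 1/12.

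The cost is five items and a visual analogue scale at a visit that already takes place, which is a minute or two of patient time, plus a minor amendment. It has to be settled before patients reach the 2-month visit, because utilities missed there cannot be recovered.
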